## **STUDY DESIGN**

Prospective, randomized, placebo controlled, double masked, cross-over clinical trial

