## **STUDY PLAN AND RANDOMIZATION**

Enrolled patients after having performed the untreated baseline 24-hour curve of IOP and blood pressure will be randomly assigned according to a 1:1 computer-generated randomization code list to one of the 2 treatment groups.

Possible treatments will be either bimatoprost 0.01% at night plus placebo in the morning or timolol 0.5% twice (morning and evening).

After 8 weeks of treatment patients will undergo a on-treatment 24-hour IOP and blood pressure curve and will be then crossed-over to the opposite treatment so that patients treated with bimatoprost 0.01% at night plus placebo in the morning will start treatment with timolol 0.5% twice daily and vice versa. After 8 additional weeks (16 weeks from baseline) a third 24-hour assessment of IOP and blood pressure will be performed.

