## **STUDY ENDPOINTS**

Primary endpoint: comparison of the mean 24-hour IOP after 8 weeks of treatment with bimatoprost 0.01% once at night plus placebo once in the morning with that after 8 weeks of treatment with timolol 0.5% twice daily.

Secondary endpoints: the comparison of the mean IOP, BP and HR at each of the 6 timepoints of the 24h curve, the comparison of the mean day (average of the 8:00, 12:00, 16:00 and 20:00 o'clock timepoints) and night (average of the 00:00 and 04:00 o'clock timepoints) IOP, BP and HR, and the comparison of the incidence of adverse events. Additionally the mean 24h systolic and diastolic ocular perfusion pressures (OPP) will be calculated and compared between groups. The ocular perfusion pressure will be calculated as the difference between either the mean 24h systolic or the mean 24h diastolic blood pressure and the mean 24h IOP.

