### **STATISTICAL ANALYSIS**

If only one eye was eligible as trial eye, that eye was included. If both eyes were eligible only the eye with highest baseline mean 24h IOP was included in the statistical analysis.

Only patients completing the baseline, 8 weeks and 16 weeks visits (24h IOP assessment visits) were included in the efficacy analysis. All randomized patients taking any amount of the study medication were included in the safety analysis.

Data have been described as mean and 95% confidence interval (CI) for continuous variables and frequencies for categorical variables. IOP data have been analysed by treatment and not by group, thus pooling data obtained from the same treatment irrespectively of the treatment sequence. A multivariate ANOVA model for repeated measures was used to test the null hypothesis that the mean 24h IOP between treatments is not different. The treatment sequence (either first bimatoprost 0.01% + placebo or first timolol 0.5% twice daily) was included in the model as fixed effect to test the interaction between drug and treatment sequence and to explore the presence of potential carry-over effects. Post-hoc between treatments comparisons have been performed by paired t-test or Wilcoxon sign rank test after normality check performed by Shapiro-Wilk test. Categorical variables such as proportions and safety variables have been analyzed using the Pearson Chi-squared test or Fisher exact test as appropriate. Statistical significance was set at the 5% level.

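### Adverse events and other proportions are compared between drugs with tests for independent groups, although most patients in this cross-over contribute a result under both drugs (secondary and safety comparisons only)

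*Protocol*

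**What the plan says.** The Study Design section describes a "Prospective, randomized, placebo controlled, double masked, cross-over clinical trial". Under Study Plan and Randomization, each patient has 8 weeks on one treatment and then 8 weeks on the other: "patients treated with bimatoprost 0.01% at night plus placebo in the morning will start treatment with timolol 0.5% twice daily and vice versa".

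Study Endpoints lists, among the secondary endpoints, "the comparison of the incidence of adverse events". Tolerability is also part of the stated purpose in the Introduction, which names conjunctival hyperemia in particular. Schedule of the Activities adds three yes/no symptom questions at each follow-up visit, on redness, dryness or foreign body sensation, and burning.

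Statistical Analysis then fixes the tests. For between-treatment follow-up comparisons: "Post-hoc between treatments comparisons have been performed by paired t-test or Wilcoxon sign rank test after normality check performed by Shapiro-Wilk test". For categorical data: "Categorical variables such as proportions and safety variables have been analyzed using the Pearson Chi-squared test or Fisher exact test as appropriate". The safety set is broad: "All randomized patients taking any amount of the study medication were included in the safety analysis". The threshold is common to all: "Statistical significance was set at the 5% level". The protocol names no paired or clustered method for categorical data.

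**The concern.** Pearson's chi-squared and Fisher's exact test, applied to a table of drug by event, treat the bimatoprost and timolol results as coming from different people. Here they come mostly from the same people. A patient prone to notice redness or burning on one drug is plausibly more likely to report it on the other. Such positive correlation makes the variance of the difference in proportions smaller than these tests assume.

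The sentence just before it in the same section uses paired tests for between-treatment comparisons, so pairing is recognised for continuous data and dropped for categorical data.

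At stake is the tolerability comparison. An overly conservative test makes a non-significant result more likely, and that can be read as no difference in adverse events. A trial of about 29 patients has little power to spare for this.

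**Working it through.** **The plan's own figure.** The only computed figure is the sample size of 29 (Sample Size Calculation), which concerns IOP. It reproduces: N = 2 × [2 × (1.960 + 0.842) / 1.5]² = 27.9, so 28 by the normal approximation against 29 stated. No figure is given for the categorical comparisons.

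**Inputs.** From the protocol: n = 29 and two-sided 5%. Assumed, because the protocol gives neither event rates nor within-patient correlation: 30% on both drugs (null), 40% versus 15% (alternative), and correlation 0 to 0.7 on a latent bivariate normal scale. All 29 patients are taken as complete pairs.

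**Formulas.** Let a patients have the event on both drugs, b on the first only, c on the second only, with x = a + b and y = a + c.

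- Planned chi-squared: X² = 2n(x − y)² / [(x + y)(2n − x − y)]. Like Fisher's test, it uses only the totals x and y.
- McNemar: (b − c)² / (b + c) referred to chi-squared on 1 df; the exact version is a binomial test of b out of b + c.

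**The planned tests cannot see the pairing.** Take assumed totals of 10 and 4 events among 29 patients. Chi-squared gives p = 0.066 and Fisher p = 0.123 however the events pair up. The paired tests depend on the split:

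| Discordant pairs | McNemar p | Exact McNemar p |
|---|---|---|
| 6 vs 0 | 0.014 | 0.031 |
| 7 vs 1 | 0.034 | 0.070 |
| 10 vs 4 | 0.109 | 0.180 |

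**Why the error rate falls.** With common rate p and within-patient correlation φ between the two yes/no results, the variance of the difference is 2p(1 − p)(1 − φ)/n. The planned tests use 2p(1 − p)/n. At 30% on both drugs, latent correlation 0.5 corresponds to φ of about 0.32, so the true variance is about 0.68 of the assumed one. The effective critical value is then 1.96 / √0.68 = 2.37 or so, which implies a true error of about 1.8%.

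**Exact enumeration.** Summing the multinomial probabilities over all tables with n = 29, without continuity correction, gives the following.

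True type I error (%), 30% on both drugs:

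| Latent correlation | Chi-squared | Fisher | McNemar | Exact McNemar |
|---|---|---|---|---|
| 0 | 4.7 | 2.5 | 4.3 | 2.5 |
| 0.2 | 3.5 | 1.7 | 4.3 | 2.3 |
| 0.5 | 1.7 | 0.7 | 4.4 | 2.0 |
| 0.7 | 0.7 | 0.2 | 4.7 | 1.4 |

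Power (%), 40% versus 15%:

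| Latent correlation | Chi-squared | Fisher | McNemar | Exact McNemar |
|---|---|---|---|---|
| 0 | 58 | 47 | 54 | 45 |
| 0.2 | 58 | 46 | 59 | 49 |
| 0.5 | 58 | 46 | 69 | 58 |
| 0.7 | 59 | 45 | 79 | 66 |

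McNemar gains about 1 point over chi-squared at correlation 0.2, 11 points at 0.5 and 20 points at 0.7. At zero correlation it loses about 4 (58 − 54).

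**The case against.** *The qualifier at the end of the sentence may allow a paired test.* It most naturally means choosing between the two tests named, and neither is paired.

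*The tests may be meant for the two sequence groups.* They would be valid there, because those groups are independent. But the sentence has no such limit, and the endpoint it serves compares drugs.

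*A statistical analysis plan may settle it.* The protocol has not left the method open. It names one that does not fit the design.

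*The practical loss may be small.* Much of this stands. A reader might infer that the plan will miss a real tolerability difference. The documents do not support that, because they give no correlation. At low correlation chi-squared does as well as McNemar or better. The exact McNemar test is itself conservative (2.0% at correlation 0.5) and there only equals chi-squared in power, at 58%.

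Nor should the point be argued from one chosen table. Take 12 of 29 against 5 of 29, with 4 patients having the event on both drugs, 8 on the first only, 1 on the second only and 16 on neither. Fisher gives p = 0.082 and exact McNemar 0.039, which looks like a reversed conclusion. But the expected counts are 8.5 and 20.5, so chi-squared would usually be chosen. It gives p = 0.043, the same verdict as exact McNemar.

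*The data are not fully paired.* This also stands. The safety set keeps anyone who took any medication, so a patient who leaves in the first phase contributes one drug only. That makes the data mostly paired; it does not make the two samples independent.

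**Conclusion.** The categorical method is wrong as written for between-drug comparisons and should be changed. The effect is confined to secondary and safety comparisons. The primary comparison of mean 24-hour IOP, its repeated-measures model and the sample size do not depend on it, and adverse event frequencies by treatment are not altered by the choice of test.

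A reader might infer that the plan risks false claims of a tolerability difference. With positive correlation, the plausible case, the reverse is true: the tests are too conservative. Only negative correlation pushes chi-squared above nominal, for example to 6.4% at 30% on both drugs with φ = −0.15.

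Under the assumed rates, the gain from McNemar's test is clear only at moderate or higher within-patient correlation. The mismatch itself needs no assumption, since it follows from the design and the tests named. The size does: it rests on assumed rates and correlations and on 29 complete pairs. Severity: should-fix.

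**What to change.** Replace the sentence on categorical variables in Statistical Analysis with three rules:

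- For patients exposed to both drugs, compare proportions between treatments with McNemar's test and report the paired risk difference with its 95% CI.
- For the full safety set, including patients with one period only, use a GEE logistic model with treatment and period, clustered by patient.
- Keep chi-squared or Fisher tests only for comparisons between the two sequence groups.

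The text should also say whether McNemar's asymptotic or exact version is used, because they differ noticeably at this sample size.

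The cost is one rewritten sentence and a little more analysis work, with no new data. The downside is slightly lower power than chi-squared if the within-patient correlation is near zero (54% against 58% in the case worked above).

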### **SAMPLE SIZE CALCULATION**

It has been estimated that the probability is 80% that a sample size of at least 29 subjects in this cross-over study will allow to detect a between treatments difference at a two-sided 5% significance level if the true difference is 1.5 mmHg or greater. This is based on the assumption that the within-patient standard deviation of the response variable is 2 mmHg.

#### **REPORTING OF ADVERSE EVENTS**

All adverse events will be reported in the study CRFs and the investigators will present within the proper time-frame a report about all adverse events that are occurred during the study. This report will be presented at the ethical committee and at the AIFA.

Serious adverse events will be promptly reported within 24-hours from the event itself by fax at the number [contact].

#### **DRUG RELATED ADVERSE EVENTS**

Any adverse reaction will be recorded as suspected to be related to the study drugs (ADR) if there is a reasonable possibility that the relationship does exist. Any ADR will be communicated to the IRCCS Fondazione Bietti at the number [name].

#### **POST TRIAL EVENTS**

Post trial events are defined as events that occur with 30 days after the study end. Patients with potential ADR that occurs after the study end will be followed-up until the events resolves or at the judgement of the investigators. Any pregnant women will be followed-up until delivery.

#### **DATA MANAGEMENT**

CRF data will be input in a master database after validation whose integrity and consistency will be warranted.

#### **ETHICAL ISSUES**

The study will be conducted according with the ethical principles of the declaration of Helsinki and its update of October 2000, Edinburgh, Scotland, UK, with the Good Clinical Practice (GCP) guidelines and with the guidelines of the "International Conference on Harmonisation (ICH)".

**Protocol number: GLC-05-10**

The sponsor IRCCS Fondazione G.B. Bietti warrants the monitoring of the research activity and the control related with this study, the audits, revisions and inspections having direct access to the source documents. The researchers have to make accessible all original study documents to confirm the consistency with the CRF data and the signature of the informed consent by the enrolled subjects.

**CONSISTENCY CONTROL**

Consistency control will be performed on the entered data. The query will be released in case of inconsistencies. Consistent data will be validated and input in the master database.
